### Sample size calculation

The pulmonary function test is the primary outcome of interest for our study and the expected clinically relevant difference for obstructive restrictive and mixed impairment using LLN and GLI reference equation as proposed by Quanjer et al. (1993). Therefore, the sample size (*n*) will be determined using G-Power statistics software (stats.oarc.ucla.edu). The power is selected at 95% = 0.95, confidence level at 5% = 0.05 and effect size of 0.35 (Figure 1), namely:

**F-tests – MANOVA:** Repeated measures, within-between interaction

**Options:** Pillai V, O’Brien-Shieh Algorithm

**Analysis:** A priori: Compute required sample size

**Input:** Effect size f(V) = 0.35

    α err prob = 0.05

    Power (1-β err prob) = 0.8

    Number of groups = 9

    Number of measurements = 6

**Output:** Non-centrality parameter λ = 31.2375000

     Critical F = 1.4522092

     Numerator degree of freedom (*df*) = 40.0000000

     Denominator df = 210

     Total sample size = 51

     Actual power = 0.8010637

     Pillai V = 0.5456570

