**FIGURE 1 F0001:**
[figure not shown]
F-test multivariate analysis of variance of within/between group interaction.

We intend to investigate the main effects, within and between interactions, for two factors, namely:

Factor A – Therapy with three levels (Therapy A, Therapy B and No Therapy)Factor B – Types of impairments (Obstructive, Restrictive and Mixed) nested within factor A

This gives 3 × 3 = 9 groups of participants from which repeated measurements are to be obtained.

We are also planning to measure three continuous outcomes at different time points of which the minimum repeated measurements are expected to be six per subject for some of the outcomes and a maximum of 36 per subject. Suppose a minimum of six repeated measures is to be obtained from each subject, in that case, it is estimated that a minimum total sample size of 51 patients is required to detect an effect size v = 0.35 with 95% confidence (5% Type I) – similar studies also expected to produce similar results about 80% of the time (Power of test 80%). In the case that during the time of data collection, the hospital experiences a high number of COPD, IPF, ILD, cystic fibrosis, thoracic cage abnormalities patients or resources permit, we are able to increase the total sample size to at most 68 subjects with a corresponding increase in the power of the test to about 95% still detecting effect sizes between 0.3 and 0.4 (see Figure 1). This translates to the possibility of recruiting between five and eight patients per group. Hence, the sample size estimates suggest that recruiting more than eight patients per group for our study will be a waste of resources.

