### Data analysis

The Statistical Package for Social Sciences (SPSS Inc, Chicago, Illinois, United Sates) version 26.0 for windows package programme will be used to analyse data. Descriptive statistics of mean, standard deviation, frequencies and percentages will be used to summarise the results. Bar charts, pie charts and histograms will be utilised for pictorial illustration. A multivariate analysis of variance (MANOVA) will be used to compare the outcome pulmonary function variables (FEV_1_, FVC, FEV_1_/FVC, PEFR) and QoL (6MWT, MRC dyspnoea scale score and PFSDQ-M score) among groups, while the Bonforreni’s *t*-test will be utilised for post hoc analysis to detect where significant changes occurred in the outcome variables. Dependent t-tests will be used to compare the pre- and post-test results within variables while independent t-tests will be used to compare the outcome variable among the study and control groups. The level of significance will be set at *p* ≤ 0.05.

The study does not potentially involve risk or harm, as all interventions can only be performed within the limit of the patient’s tolerance. However, participants may experience mild discomfort because of the exercise, including temporary muscle soreness, increased heart rate, blood pressure, sweating and dizziness. All necessary care will be in place to prevent the occurrence of any adverse event. However, in case of a report of serious adverse events (e.g. comorbidities, injuries, persistent excruciating pain, dizzy spells, headache, etc.) after the intervention or at any point during the trial, we would consider unblinding the participant to the intervention for their safety. Additionally, the participants will be instructed to report adverse events to the first author PI or the physiotherapist supervising their group. To ensure adequate supervision, participants per group to be attended in a day will be limited to a maximum of three. Arrangements will be made with the Accident and Emergency units of the research site to provide a standby medical team. The University of KwaZulu-Natal insurance scheme on clinical trials has fully covered participants in this type of study.

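### The stated 80% power is for one outcome measured six times; it is not the power of the planned multi-outcome MANOVA, which the protocol leaves undetermined

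*Protocol article*

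**What the plan says.** **Sample size calculation.** Pulmonary function is named as the primary outcome. The trial is sized with the G*Power procedure for MANOVA, "Repeated measures, within-between interaction", with the option "Pillai V, O’Brien-Shieh Algorithm". The inputs are f(V) = 0.35, "α err prob = 0.05", "Power (1-β err prob) = 0.8", nine groups and six measurements. The output is N = 51, actual power 0.8010637 and a "Numerator degree of freedom" of 40. (The lead-in sentence gives the power as 95%. The program input and the later text use 80%, the figure examined here.)

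**Text under Figure 1.** "We are also planning to measure three continuous outcomes at different time points". Some outcomes are to be measured at least six times per subject, and others up to 36 times. The six in the calculation is explained as repeated measures per subject.

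**Data analysis.** "A multivariate analysis of variance (MANOVA) will be used to compare the outcome pulmonary function variables", namely FEV1, FVC, FEV1/FVC and PEFR, together with "QoL (6MWT, MRC dyspnoea scale score and PFSDQ-M score". That makes seven variables. Bonferroni post hoc tests and dependent and independent t-tests are also planned. The Abstract calls the main analysis a repeated MANOVA.

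**Medical Research Council dyspnoea scale.** The MRC consists of five graded statements.

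**The concern.** Three parts of the protocol describe three different analyses: one outcome in the power calculation, three continuous outcomes in the text around it, and seven variables in the analysis, of which the MRC is ordinal. A power figure belongs to a particular test. If the test that was sized is not the one that will be run, the figure tells the reader nothing reliable about the trial's ability to detect an effect.

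The figure also carries weight in the plan. The text under Figure 1 uses it to argue that more than eight patients per group would be wasteful, and the Abstract expects the results to indicate which form of spirometry suits which impairment. A joint result might therefore be read against an 80% that was never calculated for it.

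**Working it through.** **Inputs**, all from the Sample size calculation: k = 9 groups, m = 6 measurements, f(V) = 0.35, so f² = 0.1225, alpha = 0.05, N = 51. The planned total of 54 comes from the Abstract.

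**Formulae** (noncentral F for Pillai's V, O'Brien-Shieh). Let p be the number of response contrasts, q = k - 1 = 8 and s = min(p, q). Then:
- df1 = p x q
- df2 = s(N - k - p + s)
- λ = s x N x f²
- V = s f²/(1 + f²)
- power = probability that a noncentral F(df1, df2, λ) exceeds the 5% critical value

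**Step 1: reproduce the plan's figure.** One outcome at six occasions has p = 6 - 1 = 5, so s = 5.
- df1 = 5 x 8 = 40
- df2 = 5 x (51 - 9 - 5 + 5) = 210
- λ = 5 x 51 x 0.1225 = 31.2375
- V = 5 x 0.1225/1.1225 = 0.5457
- critical F = 1.4522, power = 0.8011

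Every output line agrees with the protocol. N = 50 gives 0.7885, so 51 is the smallest N that reaches 80%. No term stands for the number of outcomes.

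**Step 2: the same method for multi-outcome tests.** With r outcomes over six occasions, p = 5r. With r outcomes at one occasion, p = r. The protocol does not say whether f(V) or V should stay fixed as outcomes are added, so both are shown.

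| Test across nine groups | p | df1 | df2 (N = 51) | λ (N = 51, f(V) = 0.35) | Power N = 51 | Power N = 54 | Power N = 51, V held at 0.5457 |
|---|---|---|---|---|---|---|---|
| One outcome, six occasions (as sized) | 5 | 40 | 210 | 31.24 | 0.80 | 0.84 | 0.80 |
| Three outcomes, six occasions | 15 | 120 | 280 | 49.98 | 0.74 | 0.79 | 0.43 |
| Four spirometry variables, six occasions | 20 | 160 | 240 | 49.98 | 0.60 | 0.65 | 0.33 |
| Seven variables, six occasions | 35 | 280 | 120 | 49.98 | 0.27 | 0.32 | 0.16 |
| Four spirometry variables, one occasion | 4 | 32 | 168 | 24.99 | 0.72 | 0.76 | 0.86 |
| Seven variables, one occasion | 7 | 56 | 294 | 43.73 | 0.90 | 0.93 | 0.70 |

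**Step 3: a fixed effect per affected outcome.** Pillai's trace was simulated at N = 54 for four variables over six occasions, with f(V) = 0.35 in each affected variable.
- Uncorrelated variables: power is about 27% to 29% if one variable moves, and 98% to 99% if all four do.
- Correlation 0.7 between variables: about 81% to 82% if one moves, and about 38% if all four move in the same group pattern. If all four move in differing group patterns, power is close to 100%.

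The number of variables that move, their correlation and the pattern of change together decide the result. The protocol assumes nothing about any of them. For one outcome the same simulation gives about 75% to 76% at N = 51, against the formula's 80.1%. That gap lies between two approximations and is not an error in the plan.

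**Step 4: occasions.** The MRC, 6MWT and PFSDQ-M are fortnightly over 12 weeks, which fits six occasions. The Abstract has pulmonary function assessed before and after every session, and sessions run three times a week for 12 weeks (36 sessions). One outcome analysed at 36 occasions has p = 35, and power at N = 51 is again 0.27. The stated 80% therefore fits a spirometry variable only if it is analysed at six chosen occasions.

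**The case against.** **The power is not shown to be too low.** This stands. A reader might infer from the rows for four or seven variables over six occasions that the trial is underpowered. The documents do not support that. A one-occasion MANOVA of seven variables has power 0.90 at f(V) = 0.35, and correlation can reverse the order of the simulated cases. The four spirometry variables are certainly not independent, since FEV1/FVC is computed from two of the others. A claim that added variables must dilute the test rests on an independence that does not hold here.

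**One joint test of seven variables may not be intended.** This also stands. The Data analysis section groups the variables into pulmonary function and quality of life, which may mean two MANOVAs. The seven-variable rows are one reading only. A MANOVA of four spirometry variables is still not the test that was sized.

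**Three may count instruments.** Spirometry, 6MWT and PFSDQ-M would make three if the MRC is set aside as ordinal. That may explain the wording, but the MANOVA takes in seven variables including the MRC, so the mismatch stays.

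**A null MANOVA need not be read as no effect.** A reader might infer that everything hangs on the joint test. The plan also lists single-outcome t-tests and does not make them conditional on the MANOVA.

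**Details may be in a statistical analysis plan.** The method for the MRC may well be. The stated counts and program settings disagree within this document, whatever a later plan adds.

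**Conclusion.** The point holds as a mismatch between the test sized and the test planned. The 80% at N = 51 is correct for the group-by-time interaction of one outcome at six occasions with f(V) = 0.35. It is not the power of a MANOVA of four or seven variables, and the protocol does not give the information needed to fix that power. At N = 51 with f(V) held at 0.35, the readings tabulated run from 0.27 to 0.90; with V held instead, from 0.16 to 0.86. These are ranges under stated assumptions and not estimates of the true power, and they support neither a claim that the trial is underpowered nor a claim that the calculation is wrong. The correction should be made because the figure is used to justify the size of the trial.

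**What to change.** - Name one spirometry variable (FEV1, for example) as the primary outcome and test it in its own repeated-measures model.
- State which six occasions enter that model, and that the 80% at f(V) = 0.35 refers to this single-outcome test only.
- Report the other six outcomes separately as secondary, without attaching the 80% to them.
- Replace the count of three continuous outcomes by the seven variables listed in the Data analysis section, and note that the MRC is ordinal.

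If a joint MANOVA is kept as the main test, the protocol should instead say which variables and occasions it contains, state the assumed effects and correlations, and recompute the power.

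The cost is protocol wording and slightly more analysis, with no extra patients or visits. The small downside is committing to one spirometry variable in advance.

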Following successful allocation to one of the three groups, the participants will be required to breathe in the upright sitting position before commencing the exercise using the most convenient respiration method. A volume-incentive spirometer (Coach 2 device), which enables the patient to inhale air through a mouthpiece and corrugated tubing attached to plastic bellows, will be used for the inspiratory exercise, with the volume of air displaced indicated on a scale located on the device enclosure (Kumar et al. 2016). The procedure will be demonstrated to the participant to ensure that it is well understood before commencement. After the participants have achieved the maximum volume, they will be instructed to hold the volume of air attained on the scale constant for 3–5 sec before exhalation (Zayed, Ahmed & Salem 2017). The participants will repeat the exercise three times to complete one set; three sets will be performed up to a maximum of 10 attempts. One minute of rest will be given between sets to reduce fatigue. The participants will leave after the following musculoskeletal assessment: The musculoskeletal assessment will involve screening of the participants’ musculoskeletal system for possible pain, swelling or limitation in joint range of motion. The procedure will be stopped whenever the subject feels dizziness or experience pain in the chest. The procedure will be repeated three times a week for 12 weeks. The MRC dyspnoea scale, 6MWT and PFSDQ-M will be conducted fortnightly during the study period.

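### Six fortnightly measurements in a 12-week trial cannot cover both baseline and week 12, so the schedule for 6MWT, MRC and PFSDQ-M is unclear and should be fixed at seven

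*Protocol article*

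**What the plan says.** All references are to the protocol article.

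- **Sample size calculation.** The program run lists "Number of measurements = 6", with "Number of groups = 9", "Effect size f(V) = 0.35" and "α err prob = 0.05". It returns a total of 51 and an actual power of 0.8010637.
- **Text after Figure 1.** The authors write that "the minimum repeated measurements are expected to be six per subject for some of the outcomes and a maximum of 36 per subject", and go on: "Suppose a minimum of six repeated measures is to be obtained from each subject".
- **Study Design.** The trial runs for 12 weeks.
- **Arm procedures.** The inspiratory section says "The MRC dyspnoea scale, 6MWT and PFSDQ-M will be conducted fortnightly during the study period". The expiratory and control sections say the same in substance, and the sections on the individual instruments repeat the two-week interval. None lists the assessment weeks or names a pre-treatment or week-12 assessment for these outcomes.
- **Abstract, Method.** Pulmonary function is treated differently: it is tested on both sides of each session.
- **Data analysis.** 6MWT, MRC and PFSDQ-M are listed among the outcome variables, and "Dependent t-tests will be used to compare the pre- and post-test results within variables". Pre and post are not defined.

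**The concern.** The count used for the sample size and the planned analysis do not fit together. Twelve weeks contain six two-week intervals, and six intervals have seven end points. A schedule of exactly six values drops one end of the treatment period.

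- **If week 0 is dropped**, the first value is taken after two weeks of treatment. There is then no true change from baseline and nothing to adjust for. A baseline that was not collected cannot be recovered later.
- **If week 12 is dropped**, the last two weeks of treatment are not observed and the post value is a week-10 value.

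The three outcomes stand in both specific objectives beside the spirometry variables. Baseline values matter here because each of the nine cells holds only six participants (54/9), so sizeable chance differences at baseline are likely.

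**Working it through.** **1. Counting the schedule.** Inputs: 12 weeks (Study Design), two-week spacing (arm procedures), six measurements (Sample size calculation).

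- Intervals: 12/2 = 6. Time points that include both ends: 6 + 1 = 7.
- Six values starting at week 0: 0, 2, 4, 6, 8, 10. No week 12.
- Six values starting at week 2: 2, 4, 6, 8, 10, 12. No week 0.

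The two counts in the text after Figure 1 look like planned totals for different outcomes: 36 = 3 sessions x 12 weeks, and 6 = 12/2. On that reading, six is the number planned for the outcomes measured least often.

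**2. What each dropped end leaves out.** Two weeks hold 2 x 3 = 6 of the 36 sessions, or 17%. They come before the first value if week 0 is missing, and after the last value if week 12 is missing.

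**3. Reproducing the stated sample size.** Repeated-measures MANOVA, within-between interaction, Pillai V, O'Brien-Shieh, with k groups and m measurements:

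- s = min(k - 1, m - 1)
- df1 = (k - 1)(m - 1)
- df2 = s[N - k - (m - 1) + s]
- lambda = f² x s x N
- V = s f²/(1 + f²)

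With k = 9, m = 6, f = 0.35, N = 51:

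- s = 5, df1 = 8 x 5 = 40, df2 = 5 x (51 - 9 - 5 + 5) = 210
- lambda = 0.1225 x 5 x 51 = 31.2375
- V = 5 x 0.1225/1.1225 = 0.5457
- critical F = 1.4522, power = 0.801, smallest N for 80% power = 51

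This matches the article, so its figure is right for six measurements.

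**4. The same calculation with seven.** Now s = 6 and df1 = 48; df2 = 6 x 42 = 252 at N = 51 and 6 x 45 = 270 at N = 54. The answer depends on which effect measure stays fixed when m changes.

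- *f(V) = 0.35 held:* lambda = 0.1225 x 6 x 51 = 37.485 at N = 51 and 39.69 at N = 54.
- *Pillai V = 0.5457 held:* f² = V/(s - V) = 0.5457/5.4543 = 0.1000, so f = 0.316; lambda is about 30.6 at N = 51 and 32.4 at N = 54.

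| Case | Power, N = 51 | Power, N = 54 | N for 80% |
|---|---|---|---|
| Six, as planned | 80.1% | 83.5% | 51 |
| Seven, f(V) held | 85.9% | 88.8% | 47 |
| Seven, Pillai V held | 74.8% | 78.6% | 56 |

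**5. Value of a baseline.** With six per cell, the standard error of a chance baseline difference between two cells is sqrt(2/6) = 0.58 SD. Using week 0 as covariate reduces the variance of a week-12 comparison by about r², where r is the correlation between the two values. The article gives no r. For an assumed r of 0.5 to 0.8 the reduction is 0.5² = 25% to 0.8² = 64%, leaving 1 - r² = 75% to 36%.

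**The case against.** The strongest reply is that the article never fixes the count at six. It calls six a minimum, and a minimum allows seven. The six-minute walk section speaks of repeating the test every two weeks, which fits a first test followed by six repeats, and planning a pre-test comparison suggests that a pre-test is intended. A journal article may also leave the visit table to the full protocol. Much of this stands. It means that the text does not exclude a baseline.

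A reader might infer that the pre/post analysis of these outcomes cannot be done at all. The documents do not support that. With weeks 0 to 10, a comparison of baseline with week 10 and baseline adjustment both remain possible. They are lost only if the six values are weeks 2 to 12 with no baseline, and no section says so. Nor does the point reach the primary outcome, since lung-function values exist before the first session and after the last.

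A reader might also infer that moving to seven measurements simply raises power, or simply lowers it. Neither follows, because the direction depends on whether f(V) or Pillai V is held.

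What the reply does not remove is the mismatch itself. The run uses six, six equals 12/2, no section gives a seventh value, and the analysis needs both ends. This concerns a stated count and a stated analysis, so it is more than a detail left out for brevity.

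**Conclusion.** The point holds as an inconsistency or ambiguity in the schedule of three non-primary outcomes. Taken literally, six fortnightly values lose either the baseline or the end-of-treatment value, and pre and post are undefined for 6MWT, MRC and PFSDQ-M. This should be corrected before data collection, because a missed baseline cannot be replaced.

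The effect on the sample size is modest and can go either way. The required total moves from 51 to 47 (f(V) held) or 56 (Pillai V held). Both are below the ceiling of 68 in the article, but 56 is two more than the planned 54. These figures rest on the article's own test, nine groups and alpha of 0.05. The 25% to 64% gain from baseline adjustment rests on assumed correlations and is illustrative only.

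**What to change.** 1. State seven assessments for 6MWT, MRC and PFSDQ-M: week 0 before the first session, then weeks 2, 4, 6, 8, 10 and 12.
2. For these outcomes, define pre as week 0 and post as week 12.
3. Compare groups at week 12 with the week-0 value as covariate. This goes beyond removing the inconsistency, but it is a clear improvement on unadjusted t-tests with six per cell.
4. Make the number of measurements in the power calculation match. Enter seven if all seven values go into the repeated-measures test; keep six only if the text says that week 0 stands outside that test.
5. If seven is entered, report power under both assumptions (88.8% and 78.6% at 54) and say which effect measure is taken as fixed.

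The cost is one extra assessment per participant at a visit that already takes place, and a reworded sample size paragraph. No patients are added if f(V) is held; if Pillai V is held, two more than 54 restore 80% power.

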### Procedure

#### Randomisation and blinding

The patients attending the respiratory clinic of LASUTH, Ikeja, Lagos, Nigeria, West Africa, will be approached for possible interest in participating in our study. A bulk text message captioned ‘Invitation to a study on respiratory impairments’ will be circulated to interested participants using a Luxury bulk SMS platform.

Interested potential participants will be screened by Examiner 1 (the study physician) using the inclusion and exclusion criteria to determine their suitability. If suitable, they will be assigned to three groups of 18 participants per group based on the class of respiratory impairment by research assistant 1 (RA1). A simple random sampling technique will be used to assign interested participants into three major groups (groups A, B and C): subgroup A (x, y, z), subgroup B (e, f, g) and subgroup C (h, i, j). The allocation will be performed in phases through balloting according to the class of respiratory impairment, with each participant picking a slip of paper in a ballot box containing equal pieces marked either ‘A’ ‘B’ or ‘C’ for the main group, ‘x’ ‘y’ or ‘z’ for subgroup A, ‘e’ ‘f’ or ‘g’ for subgroup B and ‘h’ ‘i’ or ‘j’ for subgroup C, based on the number of participants present (Figure 2). The first author, who is the principal investigator (PI) will generate the ballot slip, while research assistant 2 (RA2) will supervise the balloting. There will be pre-commencement training for the field workers involved in the randomisation, investigation and data collection.

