**Method:**

Fifty-four patients aged 40 years and above with obstructive, restrictive or mixed respiratory impairments attending the respiratory clinic at the Lagos State University Teaching Hospital, Ikeja (LASUTH), will be recruited and assigned to three groups of 18 participants based on the class of respiratory impairment. Participants in each category of respiratory impairment will be subdivided into three groups. A final group of six participants per class of impairment will participate in the experiment. Our study will be a double-blind, randomised control trial with two intervention groups and one parallel placebo control group. Pulmonary function will be assessed before and after every procedure while the six-minute walk test (6MWT), Medical Research Council dyspnoea scale and the Pulmonary Functional Status and Dyspnea Questionnaire-Modified will be assessed fortnightly during our study. Data will be analysed using descriptive and inferential statistics and a repeated MANOVA; *p* < 0.05.

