Diagnosis of respiratory diseases is frequently established through spirometry because pathological confirmation is invasive and not routinely available. Hence, airflow obstruction or restrictive patterns collectively referred to as respiratory impairment is often detected through spirometry (Marcus et al. 2015). In summary, respiratory conditions such as asthma and COPD are classified as obstructive diseases, while those involving the chest wall, respiratory muscles, pleura or lung parenchyma are considered restrictive in nature (Vaz Fragoso & Gill 2012).

The diagnostic criteria that define spirometry respiratory impairment are often based on the Global Initiative for Obstructive Lung Disease (GOLD) (Quanjer et al. 1993). The threshold of < 0.70 for the spirometry ratio of FEV_1_ to FVC classifies normal spirometry, airflow obstruction or restriction in the adult population (Leivseth et al. 2013, Quanjer et al. 1993, Vaz Fragoso & Gill 2012). Airway obstruction is defined with an FEV_1_/FVC ratio of < 70% and an FVC of > 80% predicted, FEV_1_/FVC ratio of > 70% and an FVC of < 80% predicted for restrictive defects, while mixed defects are identified with FVC of < 80% predicted and an FEV_1_/FVC ratio of < 70% (Mathew et al. 2016; Uzma et al. 2008).

Based on the controversies surrounding the utilisation of Inspiratory Incentive Spirometry (IIS) and Expiratory Incentive Spirometry (EIS) in the management of respiratory impairments, our study was conceived to compare the effect of inspiratory and expiratory incentive spirometry exercise on the pulmonary parameters and quality of life (QoL) of patients with obstructive, restrictive or mixed respiratory impairments and to determine the most suitable intervention for the respective respiratory impairments.

According to Parshall et al. (2012), respiratory impairment is typically established by conducting a pulmonary function test (PFT) using a spirometer and subsequently categorised as airflow limitation (e.g. COPD or asthma) or airflow restriction (e.g. interstitial lung disease or heart failure). The criteria that define this airflow limitation are based on the GOLD (Rabe et al. 2007).

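### The ballot draws lots for main groups A, B and C after patients have already been sorted by impairment class, and filling the box by attendance does not assure six patients per cell.

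*Protocol article*

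**What the plan says.** The Randomisation and blinding section describes allocation in this order.

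- After screening, "they will be assigned to three groups of 18 participants per group based on the class of respiratory impairment by research assistant 1 (RA1". This step is a classification, not a draw.
- The next sentence reads: "A simple random sampling technique will be used to assign interested participants into three major groups (groups A, B and C". Each main group has three lettered subgroups: x, y, z under A; e, f, g under B; h, i, j under C.
- "The allocation will be performed in phases through balloting according to the class of respiratory impairment". Each patient picks from "a ballot box containing equal pieces marked either ‘A’ ‘B’ or ‘C’ for the main group", with corresponding slips for the subgroup letters.
- The box is made up "based on the number of participants present (Figure 2".

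The text does not say whether A, B and C stand for classes or therapies.

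Elsewhere, the Abstract gives class first and then a three-way subdivision of each class, ending with: "A final group of six participants per class of impairment will participate in the experiment". With 54 patients and nine groups, that sentence has to mean six per therapy within each class. The Sample size calculation section confirms a 3 × 3 layout of therapy by impairment, describes impairment as nested within therapy, and expects five to eight patients per group.

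**The concern.** A patient's impairment class is a spirometric finding, and therapy is the only thing that chance can assign. The text nevertheless prescribes two draws after the sorting by class. Staff who follow it literally must either draw a label that is already settled or split the patients further than the design allows.

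The second issue is how the box is filled. Equal slips for three letters match the number present only when that number is a multiple of three. The text gives no rule for other attendances or for unused slips. With a target of only six per cell, small departures matter: a cell of four or fewer falls below the range of five to eight that the protocol itself expects. In a box of three slips, anyone who saw the first two knows the third.

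**Working it through.** **The plan's own figure.** Inputs from the Sample size calculation section are f(V) = 0.35, α = 0.05, k = 9 groups and m = 6 measurements. Then s = min(k − 1, m − 1) = 5 and f² = 0.1225.

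At N = 51:

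- λ = N·s·f² = 51 × 5 × 0.1225 = 31.2375
- numerator df = 8 × 5 = 40
- denominator df = s(N − k − (m − 1) + s) = 5 × (51 − 9 − 5 + 5) = 210
- critical F = 1.4522 and power = 0.8011

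All of these agree with the article, and 51 is the smallest N that reaches 0.80. At N = 54 (nine cells of six) the same formula gives λ = 33.075, denominator df 225 and power 0.835. The formula takes only the total, so the ballot does not alter the stated 51.

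**What the letters can mean.**

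1. *A/B/C are classes and are drawn.* If 54 patients, 18 of each class, draw from 18 slips of each letter, each main group receives on average 18 × 1/3 = 6 patients of every class, not 18 of one class. The draw contradicts the sorting.
2. *A/B/C are therapies drawn within class, and the subgroup letter is drawn too.* Either there are 3 × 3 × 3 = 27 cells of 54/27 = 2 patients, or the second draw assigns class by lot. Neither is the planned layout.
3. *Class is fixed and the subgroup letter is the therapy.* This gives 9 cells of 54/9 = 6 and follows the Abstract's order. The A/B/C slips then do nothing.

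The mirror labelling (A/B/C as therapy, subgroup letter as a class label that is not drawn) would make the subgroup slips the redundant ones. In either case only one draw belongs in the procedure.

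**Balance within a class of 18.** Two assumptions are needed because the article states neither: every session has the same number q of patients of one class (with a smaller last session where needed), and each session uses a fresh box with q/3 slips per letter, rounded up, leftovers being discarded. Results are from 40,000 simulated runs.

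| Patients per session | P(6/6/6) | P(some arm has 4 or fewer) |
|---|---|---|
| 1 | 0.04 | 0.64 |
| 2 | 0.09 | 0.43 |
| 4 | 0.10 | 0.35 |
| 5 | 0.22 | 0.11 |
| 7 | 0.15 | 0.24 |
| 3, 6, 9 or 18 | 1.00 | 0 |

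Three rows can be checked by hand.

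- *Sessions of one* are independent draws: 18!/(6!)³/3¹⁸ = 0.044.
- *Sessions of two* leave one random letter unused in each of nine boxes. Balance needs each letter unused three times: 9!/(3!)³/3⁹ = 1680/19683 = 0.085.
- *Sessions of five* leave one letter unused in each of three boxes, and a last session of three balances. Balance needs three different unused letters: 6/27 = 0.22. An arm of four arises when all three are the same: 3/27 = 0.11.

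**Predictability.** With boxes of three, the last slip of each three is known to anyone who saw the other two. That is 6 of 18 draws in a class, or one third.

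**The case against.** A reader might infer that this ballot cannot give valid, balanced or concealed allocation at all. The documents do not support that. The Abstract's order is coherent, the ballot runs by class, and a draw of equal slips within a class is a valid chance mechanism. It balances exactly when attendance is a multiple of three or when unused slips are carried over. Patients draw their own slip after the physician has screened them, and no open list is described, so the screener cannot steer the allocation. Nor does a drawn letter change anyone's spirometric class.

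Three further points stand in the plan's favour. Figure 2 is the flow diagram for this procedure and may define the letters. The protocol tolerates five to eight per group, and 51/9 = 5.67 is not a whole number, so exact sixes are not required. The phrase about simple random sampling might suggest independent draws throughout, but a box of equal slips is a different mechanism; the two coincide only for sessions of one. The limit of three participants per group per day, in the Data analysis section, concerns supervision and does not fix the size of a balloting session.

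A reader might also see a second classification rule, because Background says "Airway obstruction is defined with an FEV_1_/FVC ratio of < 70% and an FVC of > 80% predicted" while Sample size calculation speaks of "using LLN and GLI reference equation". The latter phrase is attached to the clinically relevant difference, not to how patients are classed, so it does not establish a conflict.

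What remains is the written instruction to draw A/B/C after sorting by class, and the lack of any rule for uneven attendance. A legend in Figure 2 could explain the letters, but it would not remove the extra draw from the text.

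**Conclusion.** The point holds in a limited form. The allocation text contradicts itself on whether the main group is fixed or drawn, and one of its two draws has no place in the nine-cell design. Six per cell is not assured: under discarded leftovers and constant session size, both assumed, the chance of 6/6/6 in a class runs from about 4% to 100% with session size. For the sizes examined that are not multiples of three, the chance that some arm falls to four or fewer is between 0.11 and 0.64. These are scenarios, not predictions for this trial. The last slips of a small box are guessable, which weakens concealment without abolishing it. The sample size calculation reproduces and is not affected. This should be corrected, but it does not by itself invalidate the randomisation.

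**What to change.** Rewrite the allocation paragraph as follows.

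1. Determine impairment class first, from spirometry, and state that no lot is drawn for it.
2. Delete the A/B/C ballot and define every remaining letter in the text.
3. Ballot for therapy only, from one box per class holding 18 identical folded slips: 6 IIS, 6 EIS and 6 control. Make up each box once, draw without replacement after enrolment, and carry it over between sessions until it is empty.

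This gives 6/6/6 in each class once 18 are recruited, so nine cells of six and N = 54, whatever the attendance per session. The required minimum of 51 stays as stated.

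The cost is a few sentences and the one-time preparation of 3 × 18 = 54 slips. One weakness remains: the last few draws in each class can be predicted by anyone who keeps count of the slips.
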